## Abstract

**Background:**

Anterior cruciate ligament reconstruction (ACLR) is standard practice for athletes that wish to return to high-level activities; however functional outcomes after ACLR are poor. Quadriceps strength weakness, abnormal movement patterns and below normal knee function is reported in the months and years after ACLR. Second ACL injuries are common with even worse outcomes than primary ACLR. Modifiable limb-to-limb asymmetries have been identified in individuals who re-injure after primary ACLR, suggesting a neuromuscular training program is needed to improve post-operative outcomes. Pre-operative perturbation training, a neuromuscular training program, has been successful at improving limb symmetry prior to surgery, though benefits are not lasting after surgery. Implementing perturbation training after surgery may be successful in addressing post-operative deficits that contribute to poor functional outcomes and second ACL injury risk.

**Methods/Design:**

80 athletes that have undergone a unilateral ACLR and wish to return to level 1 or 2 activities will be recruited for this study and randomized to one of two treatment groups. A standard care group will receive prevention exercises, quadriceps strengthening and agility exercises, while the perturbation group will receive the same exercise program with the addition of perturbation training. The primary outcomes measures will include gait biomechanics, clinical and functional measures, and knee joint loading. Return to sport rates, return to pre-injury level of activity rates, and second injury rates will be secondary measures.

**Discussion:**

The results of this ACL-Specialized Post-Operative Return To Sports (ACL-SPORTS) Training program will help clinicians to better determine an effective post-operative treatment program that will improve modifiable impairments that influence outcomes after ACLR.

**Trial registration:**

Randomized Control Trial NIH 5R01AR048212-07. ClinicalTrials.gov: NCT01773317

## Background

Anterior cruciate ligament reconstruction (ACLR) is standard practice for individuals that desire to return to high-level activities, but excellent outcomes are not as commonplace as previously reported [1-5]. Currently, success after ACLR is measured using return-to-sport rates, but second ACL injuries are not only common, but devastating, and have worse outcomes than primary ACLR [6-8]. Quadriceps weakness [9-11], abnormal movement patterns [4,12-16] and below normal knee function [17] are characteristic of athletes in the months following ACLR and often persist up to two years in spite of extensive rehabilitation. Neuromuscular training focusing on restoring limb symmetry and improving knee function using sports-related movements may reduce aberrant movement patterns which are predictive of second injury risk [4,12,18,19].

Risk of a second ACL injury is highest during the first year that athletes return to sports after primary ACL reconstruction [4,13,20-22]. Young females are 16 times more likely to sustain a second ACL injury after primary ACLR and the amount of participation time in high-level activities further increases this risk [23]. Risk to the contralateral limb is higher (5-24%) than the operated limb (4-15%) [4,23-28], suggesting deficits of the involved limb are not exclusively related to re-injury. Altered neuromuscular and biomechanical movement patterns are present bilaterally in response to injury and reconstruction which fails to resolve with post-operative rehabilitation. A neuromuscular training program focused on maximizing performance after ACLR may reduce the risk of a second ACL injury.

Despite current evidence-based post-operative guidelines [29-32], quadriceps strength deficits [9-11], altered biomechanics [4,13-16,33] and poor knee function [17] are reported six months and one year after surgery. International Knee Documentation Committee 2000 subjective knee form (IKDC 2000) scores continue to improve up to one year after surgery suggesting optimal knee function has not been met [17]. Despite clearance for return to sport activities by surgeons and rehabilitation specialists, quadriceps strength deficits of the involved limb compared to the uninvolved limb still exist, and movement asymmetries continue to persist [10,11,14,16].

One year after surgery only 67% of patients have attempted some sort of training or sport activity; males are more likely than females to attempt full return to sport [34]. Individuals often do not return to their pre-injury activity level for a variety of reasons; fear of re-injury being a large contributing factor [35-37]. Patients in the medium to long term after surgery (two to seven years) that have returned to their pre-injury activity level were less likely to be fearful of re-injury during athletic participation than those that had not returned to their pre-injury level [37]. Females were more fearful with poor environmental conditions during athletic participation than their male counterparts [37].

Neuromuscular training, consisting of destabilizing perturbations to both the involved and uninvolved lower extremities, has been an effective means of enhancing functional outcomes after ACL injury compared to strength training [12,38]. Neuromuscular training programs such as perturbation training (PERT) [39] before surgery reduce gait asymmetries in female non-copers [18]. After surgery, non-copers who received pre-operative PERT demonstrated improved knee excursion symmetry during gait compared to patients who received strength training [12]. However, regardless of pre-operative intervention, aberrant movement patterns persisted up to two years after surgery [14]. Pilot data from our lab strongly suggests that utilizing this neuromuscular training program after surgery will be an effective means of improving both short term outcomes (6 months), when clearance to return to sport often occurs, and medium term outcomes (1-2 years) after surgery. Successful primary ACL prevention programs utilize a combination of balance, plyometric and strengthening exercises to decrease ACL injury risk. Similarly, our ACL-Specialized Post-Operative Return To Sports (ACL-SPORTS) Training will incorporate dynamic prevention exercises and quadriceps strengthening exercises that promote symmetrical joint loading and abate abnormal movement patterns. A post-operative intervention incorporating these elements with the addition of PERT may be effective in resolving residual impairments after surgery.

The purpose of this study is to determine the effects of this ACL-SPORTS Training program on joint loading, biomechanics, and clinical and functional measures of level 1 and 2 athletes after ACLR. This body of work will further explain in detail each component of the training program as well as the methodology of this single blinded randomized control trial.

### Hypotheses

Subjects who receive standard care plus PERT after surgery will demonstrate: 1) symmetrical knee joint loading, 2) symmetrical movement patterns, 3) improved clinical and functional outcomes and 4) improved knee function compared to subjects who receive standard care. Additionally, subjects who receive standard care plus PERT will have a higher return to pre-injury level rates in the short to medium term (6 months -2 years) compared to subjects who receive standard care.

## Methods/Design

This study is a single-assessor blinded, parallel design randomized control trial that follows the CONSORT guidelines for non-pharmacological treatment studies [40]. Additional information about this study can be found at: Clinicaltrials.gov (Identifier: NCT 01773317).

### Participants

Eighty level 1 and 2 athletes (40 men, 40 women) between the ages of 13 and 55 that have undergone an isolated, unilateral ACL reconstruction will be recruited for this study. Recruiting will be done primarily through the University of Delaware Physical Therapy Clinic. Additional recruitment will consist of newspaper advertisements as well as speaking with local surgeons and rehabilitations specialists. Athletes will be eligible for study enrollment if they were participants in level 1 or 2 activities [1] ≥ 50 hrs/year at the time of their injury, plan to return to their pre-injury level of activity, are ≥ 12 weeks after surgery, demonstrate ≥ 80% quadriceps strength index and minimal knee joint effusion [41].

### Exclusion criteria

Subjects will be excluded if: (i) not regular participants in level 1 or 2 activities (< 50 hrs/yr), (ii) > 10 months after ACLR, (iii) history of previous ACLR, (iv) history of serious ipsilateral or contralateral limb injury (i.e. Tibial fx), or (v) large osteochondral defect > 1 cm^2^ (Figure 1. CONSORT Flow Diagram of Study Protocol).

**Figure 1 F1:**
[figure not shown]
CONSORT flow diagram of study proctol.

### Procedure

Once a patient has consented to be contacted by research staff, eligibility will be determined from patient chart review and patient dialogue. All testing measures will be performed at the University of Delaware Physical Therapy Clinic by the same assessor, blinded to group assignment. Enrolled study participants will complete initial baseline testing and 10 treatment sessions followed by post-training, 1 year and 2 year follow-up testing sessions. Testing will be completed no more than two weeks prior to initiation and two weeks after the completion of the 10 training sessions. Ethical approval has been obtained from the University of Delaware Human Subjects Review board. All participants will provide written informed consent to all research testing procedures.

### Randomization and allocation concealment

Enrolled subjects will be randomized to a perturbation treatment group (PERT) or a standard treatment group (STND). A statistical random number generator will be used to generate a randomization list, stratified by gender in which an equal number of female and male subjects will be assigned to each treatment group. The research coordinator will generically label the treatment assignments to group A and B to ensure blinding is maintained. This is a single-blinded study in that individuals collecting, recording and analyzing these data will be blinded to group assignment along with the primary investigator and biostatistician. Both the treating physical therapist and the patient will not be blinded to group assignment.

### Interventions

Treatment will be completed at the University of Delaware Physical Therapy clinic by the licensed staff therapists. The therapists have an average of 6.5 yrs experience (range 1 – 20 yrs). All therapists will participate in a training session involving discussion of the treatment program and how to manage changes in effusion, complaints of muscle soreness and still effectively complete the training program. A detailed protocol with visual aids and descriptions will be provided. Once training has been initiated procedural reliability will be completed by an unblinded investigator to ensure that the intervention is properly executed. An unmasked physical therapy clinic liaison will utilize a procedural reliability check list to review three treatment sessions for the first five subjects in each arm of the study. After that each subject’s chart will be reviewed once (Additional file 1). Procedural reliability less than 85% will result in contacting the treating therapist to remedy the situation. Any additional questions regarding the training program will be intercepted by the clinic liaison to ensure blinding of those responsible for data collection is maintained.

The training protocol consists of 10 training sessions with treatment delivered by a licensed physical therapist, regardless of group allocation. Biomechanical and functional data will be collected prior to initiation of the 10 training sessions, after completion of the sessions, and 1 and 2 years after surgery. The training program consists of a series of “prevention exercises”, quadriceps strengthening exercises, agility drills and either PERT training for individuals in the perturbation group or a control exercise for individuals in the STND care group. Details of these exercises are explained in further detail below.

Prevention exercises: A combination of balance, plyometric and strengthening exercises are effective in preventing initial ACL injury [30,42]. Plyometric training improves landing biomechanics in females [43] and decreases ACL injury rates [44]. Balance training not only improves lower extremity strength, but eliminates limb asymmetries [45], which are potential risk factors for ACL injury [4,46]. Strengthening programs alone do not reduce the number of ACL injuries [47], however when combined with plyometric training there is a significant reduction in ACL injuries, specifically female athletes [44]. Established injury prevention protocols were modified to develop the “prevention exercises” for this study (Table 1). Plyometric and balance exercises include triple single-legged hops, tuck jumps and box drops; strengthening exercises include nordic hamstring curls and squats with hip abduction resistance. Triple single-legged hops are done consecutively, forward and backwards as well as laterally. The initial drill will be completed by hopping over a line on the floor and progressed to hopping over 2 inch cups and ultimately 6 inch hurdles. Progression and cueing will be given by the treating therapist as per the patient’s ability level with a training protocol as a guide (Table 1). Tuck jumps will not be completed until treatment sessions 7-10 to ensure that patients are able to tolerate jump landings safely and successfully. Box drops begin bilaterally and progress to unilateral jumps (involved limb to involved limb). Focus on mechanics during double limb tasks initially allows for an effective progression to single limb tasks [48]. The box height will be progressively increased by the treating therapist as per the patient’s ability level using the training protocol as a guide (Table 1). This task will be completed in front of a mirror for visual feedback while the therapist provides verbal cues. Proper mechanics will be required including symmetrical limb takeoff and landing for bilateral tasks, good trunk control and neutral frontal plane knee alignment during takeoff and landing for bilateral and unilateral tasks. Nordic hamstring exercises will be completed on a low mat table with the therapist stabilizing the patient’s ankles. Initially this eccentric hamstring activity will be done to about 30-45 degrees of knee flexion and repetitions as well as knee flexion angle will be progressed over the 10 training sessions. Resisted squat exercise will be done with a thera-band around the patient’s knees to facilitate hip abduction. The resistance of the thera-band will increase as tolerated by the patient and additional upper extremity tasks such as a ball toss will be added to increase the difficulty of the task and challenge the patient. These exercises will be executed with the patient wearing a rigid functional knee brace if one has been prescribed by the surgeon. If a patient will be returning to sport without a knee brace then all testing and training sessions will be done without a brace.

**Table 1 T1:** ACL-SPORTS training protocol (2 times/wk)

	**Session 1-3**		**Session 4-6**	**Session 7-10**
**Nordic Hamstrings**	Partial 2 x 5		Partial 3 x 5	Partial 3 x 5
Kneeling on mat table, therapist stabilizing feet	(~30-45°)		(~30-45°)	(>60°)
**Standing Squat**	Session 1: 3x10 with focus on proper technique	3 x 10	3 x 10	
Must squat to knees at 90 degrees, tapping chair/table/box with gluts		Add t-band around knees	progress t-bands to black	X
**Drop jumps****	3 x 10 BLE’s to BLE’s		3 x 10 BLE’s to involved limb	3 x 10 Involved limb to involved limb off box
In front of mirror, monitor proper form with landing	Jump off appropriate height (4-6-8 inch)			
			Jump off appropriate height (4-6-8 inch)	Jump off appropriate height (4-6-8 inch)
**Triple single leg hopping****	Forward/backward x10*		Forward/backward x15*	Forward/backward x15*
	Side to side x10*		Side to side x15*	Side to side x15*
	No object		Add low object to jump over (2 inch cups)	Increase height of object, appropriate for the pt. (4 inch cups or 6 inch hurdles)
This is for proper landing, NOT distance				
**Tuck jumps****				2 sets, 10-20 sec
Proper form knees to 90°	X		X	Progress to 3 sets, 20-30 seconds each

**Brace worn if surgeon requires post-op functional brace for RTS activities. *1 rep= 3 consecutive hops forward, 3 hops backward or 3 consecutive hops laterally.

Quadriceps strengthening: The results of baseline testing measures will be used to determine the patient’s need for quadriceps strengthening during the 10 training sessions. A patient that demonstrates > 90% quadriceps strength index (involved limb strength/uninvolved limb strength × 100) will not be required to complete quadriceps strengthening exercises during training, but they may continue their prior gym program. All other patients with 80-90% quadriceps strength index will complete three quadriceps strengthening exercises during three of the first six training sessions including but not limited to, lateral step downs, leg press, LAQ and isokinetic strengthening. After the 6^th^ training session the patient will be given a home strengthening program because of the progressive nature of the program and the advanced level of tasks during the last 4 sessions.

Agilities: Agility drills will be completed as per the University of Delaware guidelines. Drills will be initiated at 50% maximum effort and progressed to 100% effort and maximum speed over the 10 training sessions. Three to four agilities drills will be completed at each training session including forward/backward running, side shuffles, cariocas, figure eight’s, circles and 90 degree turns. The treating therapist will determine which agility drills to use based on the patients sports participation and ability level. Progression of these drills will include eliminating linear drills, adding more advanced multidirectional drills and utilizing a ball consistent with the patient’s sport of participation.

Perturbation training group: Patients randomized to the PERT group will complete additional PERT training as per Fitzgerald et al. [38]. PERT training is a neuromuscular training program that includes a series of progressive perturbations on unstable surfaces in both bilateral and unilateral stance. These are progressed as per patient tolerance in both magnitude and speed. Verbal distraction as well as the addition of simultaneous upper extremity or lower extremity tasks with perturbations will be used to target the individuals sport and challenge the athlete.

Standard treatment group: Patients in the STND group will complete an additional single leg balance task with added hip flexor resistance (Figure 2). This exercise will not be progressed to unstable surfaces to ensure that similar neuromuscular effects are not seen in this group. This exercise will only increase in duration and thera-band resistance (Table 2). All treatment sessions, regardless of group, will take about 1.5-2 hours to complete.

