### Secondary outcome measures

Return to sport rates, re-injury rates and return to pre-injury level of activity rates will be evaluated 1 and 2 years after surgery. Electromyography measures will be collected simultaneously with gait variables and will be used to further analyze muscle timing, co-contraction and activation patterns before and after the intervention as well as 1 and 2 years after surgery. IKDC 2000, Tampa Scale of Kinesiophobia (TSK-11), Knee Injury and Osteoarthritis Outcome Score (KOOS) including all 5 subsets and the Marx Activity Rating Scale (MARS) are additional patient reported outcome measures that will be collected at all-time points.

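### Time since surgery varies widely at the post-training test but is left out of the clinical ANOVA, and the return-to-level hypothesis starts at 6 months although its rates are assessed only at 1 and 2 years

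*Protocol article*

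**What the plan says.** All references are to the Protocol article.

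- **Entry.** Participants requires that patients "are ≥ 12 weeks after surgery". Exclusion criteria removes those "> 10 months after ACLR".
- **Training.** Interventions: "The training protocol consists of 10 training sessions". The heading of Table 1 gives the frequency: "ACL-SPORTS training protocol (2 times/wk".
- **Tests.** Procedure allows up to two weeks between baseline testing and the first session, and up to two weeks between the last session and post-training testing. Interventions then places the later tests "after completion of the sessions, and 1 and 2 years after surgery".
- **Hypothesis.** Subjects given perturbation training are expected to have a "higher return to pre-injury level rates in the short to medium term (6 months -2 years".
- **Assessment of that hypothesis.** The section on secondary outcomes fixes the timing: "Return to sport rates, re-injury rates and return to pre-injury level of activity rates will be evaluated 1 and 2 years after surgery".
- **Randomisation and analysis.** Randomisation is stratified by gender only. Data and statistical analysis specifies ANCOVA for gait measures without naming the covariates, and ANOVA for clinical variables. Group is the between-subjects factor and time the within-subjects factor.

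**The concern.** Two separate matters meet in the visit schedule.

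First, the post-training test is tied to the end of training, while the later tests are tied to surgery. With a wide entry window, patients tested at the same nominal visit are at very different stages of recovery. Background says that IKDC 2000 scores go on improving up to one year after surgery, so recovery is still under way across this window. Spread in entry time then adds variance to the outcomes. A chance difference between arms in entry time would also go unadjusted in the clinical models. What is at stake is precision and protection against chance imbalance.

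Second, one stated hypothesis covers a period whose early part has no assessment of the rate it concerns. A report that repeated the hypothesis as worded would claim more than the data can show.

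**Working it through.** The plan gives no figure of its own to reproduce here, so the check is calendar arithmetic followed by a comparison of sections.

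**Inputs.** Earliest entry is 12 weeks (Participants) and latest entry 10 months (Exclusion criteria). Ten sessions at two per week take 4.5 to 5 weeks (Interventions, Table 1). The waits before and after training are 0 to 2 weeks each (Procedure). One year is 365.25/7 = 52.2 weeks and one month is 4.348 weeks, so 10 months is 43.5 weeks. I assume that entry is the baseline test and that training is not held.

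**Formula.** Post-training test = entry + wait before + training + wait after. The added time is 0 + 4.5 + 0 = 4.5 weeks at the shortest and 2 + 5 + 2 = 9 weeks at the longest.

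| Entry | Post-training test (weeks after surgery) | Gap to 1-year test (weeks) |
|---|---|---|
| 12 weeks | 16.5 to 21.0 | 35.7 to 31.2 |
| 6 months (26.1 weeks) | 30.6 to 35.1 | 21.6 to 17.1 |
| 10 months (43.5 weeks) | 48.0 to 52.5 | 4.2 to −0.3 |

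**How rare is true overlap?** Without a hold, it needs entry after 52.18 − 9 = 43.18 weeks, the last 0.3 week of a window of 43.48 − 12 = 31.48 weeks, and the full 9-week delay as well. If entry were uniform over the window (an assumption; the document gives no distribution) and every patient took the full delay, 0.3/31.5 is about 1%. At the mid-range delay of 6.75 weeks nobody overlaps. The two tests then fall within 4 weeks of each other for entry after 52.18 − 4 − 6.75 = 41.43 weeks, or 2.05/31.48, about 6.5%. Training can be held for effusion with no stated maximum duration, which would raise these shares.

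**How large could a chance imbalance be?** Under the same uniform assumption, the SD of entry time is 31.5/√12 = 9.1 weeks. With 40 per arm, the standard error of the difference in mean entry time is 9.1 × √(1/40 + 1/40) = 2.0 weeks. Differences up to about 1.96 × 2.0 = 4 weeks would be unremarkable.

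**The 6-month claim.** The scheduled tests are baseline, post-training, 1 year and 2 years. Return-to-level rates are listed for the last two only. The post-training test does not stand in for 6 months: it falls at 26.1 weeks only for entry between 26.1 − 9 = 17.1 and 26.1 − 4.5 = 21.6 weeks. With uniform entry and a 5-week interval, about 8/31.5 = 25% of patients would have it within 4 weeks of 6 months.

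**The case against.** The wide entry window is deliberate. The Discussion says that training starts on clinical criteria rather than at a fixed time, so patients are aligned on function at entry. Visits can be treated as nominal levels of a within-subjects factor, the 1- and 2-year tests share a common time since surgery, and randomisation balances entry time on average. All of this stands. The arms remain comparable at every visit.

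A reader might infer that the post-training and 1-year tests routinely coincide for late entrants, or that the time factor is invalid and follow-up should be counted from randomisation. The documents support neither. Overlap is an extreme case, and anchoring to surgery or to randomisation is a trade-off, not an error. A reader might also infer that the post-training test is presented as a 6-month test; the protocol never labels it so.

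It can be said, too, that covariates and visit windows belong in an analysis plan that is not shown. For the gait ANCOVA that is fair, since its covariates are simply unnamed. It does not cover the clinical variables, for which the article itself specifies an ANOVA.

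On the hypothesis, 1 and 2 years do lie inside the stated period, and the outcome is secondary. The Marx Activity Rating Scale is collected at every time point, and return-to-sport criteria are tested after training. These give short-term activity and clearance data, but neither is the return-to-level rate.

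**Conclusion.** The point holds as two modest defects.

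- **Time since surgery.** The post-training test spans about 16.5 to 52.5 weeks after surgery, and the gap to the 1-year test runs from about 36 to about 4 weeks, with none only in the extreme case. The consequence is avoidable variance and exposure to chance imbalance, not systematic bias. The timing range assumes no training holds. That time since surgery is prognostic in these patients is likely from the Background statement but is not quantified, so the gain in precision cannot be computed from the document.
- **Hypothesis wording.** The 6-month end of the return-to-level hypothesis has no matching assessment. The hypothesis can still be tested at 1 and 2 years, so it would be too strong to call it untestable; only its short-term part is unsupported.

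Both are worth correcting because the remedies are cheap.

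**What to change.** (a) Add weeks from surgery to baseline as a covariate in the gait ANCOVA, and replace the clinical ANOVA with an ANCOVA that includes it. The value is already known from the eligibility check. Let its slope differ by visit: in a repeated-measures model, a covariate with one common slope does not alter the group-by-time comparison. The cost is one degree of freedom, plus one for each further visit if the slope varies.

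(b) Either restate the return-to-level hypothesis for 1 and 2 years after surgery, or record return-to-level status at the existing post-training test and describe that result as end of training. Restating is the cleaner option. Clearance criteria are first applied after training, so the rate at that test may be low and say little. Either way no visit is added, and the price is that the 6-month claim is narrowed.

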### Data and statistical analysis

Differences between groups will be analyzed using an analysis of covariance (ANCOVA) for biomechanical gait measures and an analysis of variance (ANOVA) will be used for clinical variables. Group assignment will be blinded to the researcher using A and B variables. Assumptions of ANOVA testing will be confirmed prior to statistical analysis. Training group randomization will be used as the between-subjects factor with a within-subjects factor of time. A significance level of p < 0.05 will be set a priori.

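### Baseline quadriceps index decides who gets strengthening but is neither a stratum nor a term in the clinical ANOVA: a minor, cheaply recovered loss of precision, not a bias

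*Protocol article*

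**What the plan says.** All references are to the protocol article.

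- **Eligibility (Participants).** Patients must "demonstrate ≥ 80% quadriceps strength index and minimal knee joint effusion".
- **Who is strengthened (Interventions, quadriceps strengthening paragraph).** "The results of baseline testing measures will be used to determine the patient’s need for quadriceps strengthening during the 10 training sessions". Above 90%, patients "will not be required to complete quadriceps strengthening exercises during training, but they may continue their prior gym program". For the rest, "All other patients with 80-90% quadriceps strength index will complete three quadriceps strengthening exercises during three of the first six training sessions", followed by a home programme after the sixth session. With the floor of 80%, the rule divides the whole enrolled population in two. It makes no reference to treatment arm.
- **Randomisation (Randomization and allocation concealment).** The list is "stratified by gender in which an equal number of female and male subjects will be assigned to each treatment group". No other stratification factor is named.
- **Analysis (Data and statistical analysis).** The methods are "analysis of covariance (ANCOVA) for biomechanical gait measures and an analysis of variance (ANOVA) will be used for clinical variables". The factors are given as follows: "Training group randomization will be used as the between-subjects factor with a within-subjects factor of time". The covariate of the gait ANCOVA is not named.
- **Outcomes (Outcomes measures).** The clinical outcomes are among the primary ones. They include the quadriceps index itself, four hop tests and patient-reported measures.

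**The concern.** A baseline measurement decides part of the treatment that a patient receives, and it probably predicts the strength-related outcomes as well. Such a variable is a natural candidate for the randomisation or the model. Here it is in neither, at least for the clinical outcomes, where the article commits to an ANOVA on group and time.

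Two things could follow. Variation between the two index groups stays in the error term, so the PERT versus STND comparison is less precise than it could be. And if one arm happens to contain more patients at 80-90%, the stated model does not correct the estimate for that. The variable is already measured in every patient, so the loss is avoidable.

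**Working it through.** **Inputs from the article.** 40 patients per arm; alpha 0.05; power 80%; effect size 0.3; 72 patients needed and 80 enrolled after 10% dropout (Sample size).

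**Assumed inputs, not in the article.** The share of patients at 80-90%, p, is taken as 20-60%. The gap between the two index groups on the analysed quantity, δ, is taken as 0.3-0.8 within-group SD.

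**The plan's own figure.** 72/0.90 = 80, as stated. The metric of the effect size is not named. Read as Cohen's f, 0.3 means d = 0.6, and an exact one-sided t-test then needs 36 per arm, or 72. A two-sided two-group F-test needs 90. Nothing below depends on which was meant; d = 0.6 serves only as a yardstick.

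**Step 1: chance imbalance.** The SD of the arm difference in share is √(2p(1−p)/40).

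- p = 0.2: √(0.32/40) = 0.089
- p = 0.5: √(0.50/40) = 0.112
- p = 0.6: √(0.48/40) = 0.110

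The SD is therefore about 9 to 11 percentage points. By exact binomial calculation, a gap of at least 10 points (4 of 40 patients) has probability 33-43%, and a gap of at least 20 points has probability 3.5-9%.

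**Step 2: what a realised imbalance does.** Shift of the estimate = gap × δ. For a 20-point gap, 0.20 × 0.3 = 0.06 SD and 0.20 × 0.8 = 0.16 SD, that is 10% and 27% of d = 0.6. The standard error of the arm difference is √(2/40) = 0.22 SD, so even this uncommon gap moves the estimate by less than one standard error.

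**Step 3: average effect and precision.** Over repeated randomisations the shift averages zero. Its variance is 2p(1−p)δ²/40. Relative to the within-group variance of the arm difference, 2/40, that is p(1−p)δ². This is exactly the share by which omitting the index inflates the variance. Chance shift and lost precision are therefore one quantity and must not be added. At p = 0.5 the inflation is 0.25 × 0.09 = 2% for δ = 0.3, 0.25 × 0.25 = 6% for δ = 0.5, and 0.25 × 0.64 = 16% for δ = 0.8.

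Simulation of 40,000 trials per setting, one analysed value per patient, 40 per arm, two-sided 5% test, d = 0.6:

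| δ (SD) | p | Power, group only | Power, index group added |
|---|---|---|---|
| 0.3 | 30% | 74.9% | 75.3% |
| 0.3 | 50% | 74.8% | 75.1% |
| 0.5 | 30% | 73.5% | 75.1% |
| 0.5 | 50% | 72.4% | 74.7% |
| 0.8 | 30% | 70.0% | 74.8% |
| 0.8 | 50% | 69.4% | 75.3% |

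With no treatment effect, rejection rates were 4.9-5.2% without the term and 4.9-5.1% with it. The mean unadjusted estimate was within 0.003 SD of the truth throughout.

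Hand check of the last row: 0.6 × √20 = 2.683 with the index in the model, and 2.683/√1.16 = 2.491 without it. The normal approximation gives Φ(2.683 − 1.96) = 76.5% and Φ(2.491 − 1.96) = 70.2%, also a loss of about 6 points.

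**Step 4: how the index must enter the model.** In a balanced repeated-measures ANOVA, the group-by-time contrast compares the arms on change from baseline. A term γ·(index group) that is constant over time cancels in each patient's change. A main effect alone therefore leaves that contrast as it was. The index helps only if its effect may differ by visit, or if the follow-up value itself is modelled.

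**The case against.** The strongest reply is that this is no design error. The rule uses a baseline value and is applied identically to PERT and STND, so strengthening belongs to the common background programme. A chance difference in the share at 80-90% is an ordinary covariate imbalance, which the standard error already allows for. This stands, and it limits the point to precision. A reader might infer that PERT is confounded with strengthening or that type I error is inflated. Steps 2 and 3 show neither.

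Other parts of the reply also stand:

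- **Gait and joint loading.** A reader might infer that the index is missing from every primary analysis. The gait ANCOVA has an unnamed covariate, and that detail may sit in an analysis plan that is not shown. Absence is established only for the clinical ANOVA.
- **The treatment contrast.** It would be too strong to say that patients above 90% get no strengthening. They are merely not required to do it, may keep up their own gym work, and do the squats in Table 1 like everyone else.
- **Direction of the gap.** Strengthening goes to the weaker group. If it works, it may narrow the difference between index groups and so reduce variance. No figure in the article supports a large gap.
- **The abstract.** "A standard care group will receive prevention exercises, quadriceps strengthening and agility exercises" might be read as contradicting the conditional rule. It is condensation; the Interventions section supplies the condition.
- **The quadriceps index as outcome.** Its baseline is already one level of the time factor, so the gain lies mainly with the hop and self-report measures.

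What does not stand is that the whole matter belongs to an unseen analysis plan. For the clinical variables the article makes a choice: ANOVA rather than ANCOVA, with the factors named.

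**Conclusion.** The point holds as a minor one. The baseline index that decides who is strengthened is not a stratification factor and is not named in the model fixed for the clinical outcomes. The consequence is a loss of 0 to about 6 power points, negligible at a gap of 0.3 SD and largest at 0.8 SD. A chance imbalance with an SD of about 9 to 11 percentage points also stays unadjusted in the trial that is actually run. There is no average bias and no inflation of type I error.

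The size rests on assumptions that the article cannot confirm: the share of patients at 80-90%, the net gap between index groups on the quantity analysed, and d = 0.6 as reference. If the gap is small, or strengthening closes it, almost nothing is lost.

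**What to change.** In Data and statistical analysis, pre-specify baseline quadriceps index as a covariate for the clinical outcomes, chiefly the hop and self-report measures. Continuous is preferable; the 90% cut-off is acceptable. Enter it in one of two ways:

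1. in the repeated-measures model together with its interaction with time; or
2. in an ANCOVA of the follow-up value that also includes the outcome's own baseline. When the outcome is the quadriceps index, the two covariates are the same variable.

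State whether the index is also a covariate in the gait ANCOVA. Report strengthening received by arm. Separate PERT estimates within each index group are not needed: they would split about 40 per arm further and settle nothing.

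The cost is small. The ANCOVA spends one degree of freedom on the index. The repeated-measures version spends one, plus three for the interaction over the four test times. No new data are needed for the covariate, and neither the randomisation nor the strengthening rule has to change.
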